### 3 OUTCOME MEASURES

| Objectives                                                                                                                                                                                                       | Outcome Measures                                                                                                                                                                     | Timepoint(s) of evaluation of this outcome measure (if applicable)                                                                                                                                 |
|------------------------------------------------------------------------------------------------------------------------------------------------------------------------------------------------------------------|--------------------------------------------------------------------------------------------------------------------------------------------------------------------------------------|----------------------------------------------------------------------------------------------------------------------------------------------------------------------------------------------------|
| 
Primary Objective
 
To describe how the gut microbiota changes over time in a cohort of individuals aged 60 years and older without existing serious health conditions on study entry.
 | 
Profile of the structure and composition of the bacterial component of the gut microbiota in a cohort of ageing individuals without serious health conditions.
                | 
Samples collected at start of study (t=0) and at 6 monthly intervals up to 48 months with sample analysis ongoing throughout the study.
                                                     |
| 
Secondary Objectives
 
1. Establishment of the study cohort and sample repository to facilitate future research into ageing.
                                                           | 
Successful recruitment to all three study groups.
 
Obtain all samples from individual participants according to procurement schedule. Deposit samples in Biorepository.
 | 
Recruitment completed within 24 months of study start date.
 
Sample repository initiated from study start date with further collections at 6 monthly intervals up to study end point.
 |

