This subgroup will require at least 30 participants from each cohort to have colonic biopsies taken. Based upon previous and ongoing studies at QIB using human biopsy samples, this number of participant samples is sufficient to provide the required number for various downstream analyses and production of robust data sets to establish structural and functional profiles of tissue-associated microbial and host cell populations. This will enable us to formulate testable hypotheses to undertake future mechanism-based research. Over the period 01/01/2019 to 31/12/2021 the NNUH-QI Endoscopy department is scheduled to carry out bowel cancer surveillance colonoscopy procedures on approximately 1,400 patients from which we would recruit participants to this subgroup. We are confident therefore in obtaining the required number of biopsies for our study. See Section 7.2.

Participants from Stream 2 will be having a routine care surveillance colonoscopy which may or may not include the need for routine clinical biopsies to be taken. Participants in this study will have, in addition to any routine clinical care biopsies, and when possible 6-8 pinch biopsies each measuring 3mm^3, taken from the large bowel for research purposes. If any routine biopsies need to be taken as part of the CSP clinical care, research biopsies will only be taken after the routine care biopsies have been taken. It is acknowledged that it may not be possible to achieve the minimum of 6 biopsies in some cases. Consent for the routine care colonoscopy and the procedure will be performed by [name] or a member of his team.

For participants enrolled on to the study from Stream 2, the design of the CSP lends itself for potentially obtaining a second set of colonoscopy biopsies (provided the participant is in agreement). This is possible because the participant will be placed in the 1 year or 3 year waiting list for their next colonoscopy and is dependent on clinical findings from the first BCSP colonoscopy (study duration from the Baseline

visit is 48 months). It is acknowledged that some participants may have completed several Study Visits or are nearing the end of the study by the time they have undergone a colonoscopy as part of the BCSP.

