## 8 Phase 1 - Screening and Recruitment Phase

### 8.1 Telephone Contact

Once a reply sheet from a participant from Stream 1 (Annex 8.1) or Stream 2 (Annex 8.2) is received, they will receive an initial telephone call from the QIB Researcher. If a reply sheet is received from a participant from Stream 3 (Annex 8.3), they will receive the initial telephone call from a NSFT Research Nurse. Each participant will receive an overview of the study requirements and any questions will be answered. The Study Researcher will use the Telephone Contact section of the Telephone Contact/Pre-Study Visit Checklist (Annex 9) as a guide to providing all study information and checking eligibility before making the Pre-Study Visit appointment. It is anticipated that the Telephone Contact call will last approximately 20 minutes. If the participant is unsure of their medical history, they can check this with their GP and let the Study Researcher/NSFT Research team know before the Pre-Study Visit appointment is made.

If the participant has received antibiotics within 14 days, or a vaccination within 28 days of the planned Pre-Study Visit, the Pre-Study Visit will be delayed for the

appropriate washout period (antibiotics is 14 days from the date of the last dose and 28 days from the date of the last vaccination). This will ensure a baseline consistency at the point of consenting at the Pre-Study Visit. Any other circumstances which may delay the Pre-Study Visit from being booked will be discussed on an individual basis.

If the participant is not eligible to participate, they will be given the reason why and thanked for their time and interest in the study.

If the participant is eligible and is happy with the study requirements, the Pre-Study Visit appointment will be made.

For Stream 1 & 2, participants will attend the QI CRF. For Stream 3 participants, they will be seen in their own home by the NSFT Research Nurse as it is acknowledged that they would feel more comfortable. During the Telephone Contact discussion, the participant will be made aware that the Pre-Study Visit will last up to 2.5 hours and that during this time, the Study Researcher/NSFT Research Nurse will do the following: -

- ✚ Go through all elements of the study in full detail.
- ✚ Go through the Participant Instructions for Stool Collection (Annex 13) and the Participant Stool Sample Collection Log (Annex 14).

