## 9.1 Study Visits

### 9.1.1 Baseline Visit (approximately up to 3 weeks from Pre-Study Visit).

The participant will be provided with their Study Appointment Schedule (Annex 19) and a Study Identification carry card (Annex 20). The Study Researcher will go through these with the participant. The participant will also receive a freezer magnet displaying the study logo. This will act as a reminder for the participant to freeze their ice-packs ahead of stool sample collection. Participants will be informed that they will be sent a one-page newsletter either via an online link (Annex 38) or provided as a hard copy at the appropriate study visit to provide recruitment updates, study reminders and sign post participants to related information of interest.

This visit will take approximately 2 hours. Participants will be required to attend the QI CRF for their Baseline Visit for the following: -

[figure not shown] Undergo Cognitive tests and associated Questionnaires (see Section 11.3.1 for full description): -

- ❖ Mini ACE – repeated again at this visit for reliability
- ❖ CCI – repeated again at this visit for reliability

- ❖ PHQ 9 (Patient Health Questionnaire)
- ❖ Supermarket Test
- ❖ Sea Hero Test
- ❖ CBI-R (participant)
- ❖ RCFT (Rey Complex Figure Test)
- ❖ TMT (Trail Making Test)
- ❖ BPQ (Body Perception Questionnaire)

The CCI, PHQ9, CBI-R and BPQ are self-administered tests. The remainder activities are delivered by the Study Researcher.

- ✚ Complete the Full Health Questionnaire.
- ✚ Obtain Blood sample – 40 ml (8 teaspoons).
- ✚ Collect physical measurements (height, Tanita scales measurement, BP and hand grip strength measurements).
- ✚ Discuss the OCT/OCT (A) scan and brain MRI scan (as appropriate) appointment as below. Participants will be made aware that they would need to allow up to 1.5hrs for the brain MRI and up to 3 hours for the OCT/OCT (A) scan.

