### 11.8 Drop-off & collection of the stool collection pack.

The Baseline Visit stool collection pack will be given to the participant at the end of the Pre-Study Visit and the Study Researcher providing this will go through the collection instructions with the participant.

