### 13.1.2 Stool sample

#### **Why are we collecting these samples?**

Gut microbes influence many important processes in the body including the digestion of food, programming of the immune system, and helping to prevent invasion of pathogenic microbes. Importantly, these microbes change during [39]ageing with these changes being associated with declining physical and mental health. Identifying microbes from stool samples allows us to determine: 1) which constituent members of the gut microbiome are changing and when: 2) what relationships there are between these changes and a deteriorating function of other organ systems (e.g. the brain, eyes, heart, liver, kidneys, bone and thyroid): 3) how different lifestyle and behavioural factors (e.g. medications) may contribute to changes in microbe populations.

Stool samples are taken to examine the microbiome content. Participants will produce their samples at home and bring it to the QIB within 24 hours of their scheduled study visit. They will also have the option of providing a sample within 24 hours after their scheduled study visit. Participants will be provided with their stool collection pack with full collection instructions (Annex 13). There will also be a AnaeroGen sachet for oxygen expulsion. Two days before the participant is due to produce their sample, participants will be requested to freeze their 3 ice-packs, so

they are frozen in good time. Participants will be requested to place their bagged stool sample between the ice-packs in order to preserve the integrity of the sample and the viability of as many microorganisms as possible until the sample is brought to QIB by the participant. The collection protocol has been developed according to International Human Microbiome Standards (IHMS) guidelines [39].

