## 27 Schedule of Events (Annex A)

|                                                      | PHASE 1 Study Schedule |                 | Phase 2 Study Schedule                                                     |                  |                  |                  |                  |                  |                  |                  |                                                         |
|------------------------------------------------------|------------------------|-----------------|----------------------------------------------------------------------------|------------------|------------------|------------------|------------------|------------------|------------------|------------------|---------------------------------------------------------|
|                                                      | Telephone Contact      | Pre-Study Visit | Baseline Visit                                                             | Study Visit 1    | Study Visit 2    | Study Visit 3    | Study Visit 4    | Study Visit 5    | Study Visit 6    | Study Visit 7    | Study Visit 8                                           |
|                                                      |                        |                 | Up to 3 weeks from Pre-Study Visit                                         | 6m +/- 1 month   | 12m +/- 1 month  | 18m +/- 1 month  | 24m +/- 1 month  | 30m +/- 1 month  | 36m +/- 1 month  | 42m +/- 1 month  | 48m +/- 1 month                                         |
|                                                      |                        |                 |                                                                            |                  |                  |                  |                  |                  |                  |                  |                                                         |
| Telephone Call                                       | X                      |                 |                                                                            |                  |                  |                  |                  |                  |                  |                  |                                                         |

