| Health Questionnaire                                 |                        |                 | X 6*                                                            | X 6*  | X 6*  | X 6*  | X 6*  | X 6*  | X 6*  | X 6*  | X 6*                                         |
| Brain MRI Scan                           |                        |                 | X
within 6 weeks from Baseline                                          |                  |                  |                  |                  |                  |                  |                  | X
within 6 weeks before Study Visit 8                |
| Physical Measurement Collection          |                        |                 | X*                                                                         |                  | X*               |                  | X*               |                  | X*               |                  | X*                                                      |
| Electronic Frailty Index Data Collection from GP     |                        |                 |                                                                            |                  |                  |                  |                  |                  |                  |                  | X                                           |
| Colonoscopy Tissue Biopsy               |                        |                 | Stream 1 Endoscopy at any time point during the study                      |                  |                  |                  |                  |                  |                  |                  | Collection at                                           |
|                                                      |                        |                 | Stream 2 Endoscopy between Pre-Study Visit and Study Collection (Baseline) |                  |                  |                  |                  |                  |                  |                  | 2 time points                                           |

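### The Schedule of Events places the Stream 2 colonoscopy just before the Baseline stool sample, with no minimum interval, pre-procedure sample or flag to protect the t=0 microbiota profile

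*Protocol*

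**What the plan says.** - **Timing of the procedure.** All of Stream 2 is scheduled for colonoscopy: "Participants from Stream 2 will be having a routine care surveillance colonoscopy" (Section 5.2.1). The Schedule of Events gives its place as "Stream 2 Endoscopy between Pre-Study Visit and Study Collection (Baseline" and heads the Baseline column "Up to 3 weeks from Pre-Study Visit" (Section 27).
- **Timing of the stool.** "The Baseline Visit stool collection pack will be given to the participant at the end of the Pre-Study Visit" (Section 11.8). Section 13.1.2 then says: "Participants will produce their samples at home and bring it to the QIB within 24 hours of their scheduled study visit". It also allows a sample within 24 hours after the visit.
- **Role of the stool.** The time points for the primary outcome are "Samples collected at start of study (t=0) and at 6 monthly intervals up to 48 months" (Section 3). Baseline composition also feeds the cross-sectional Questions 1 to 5 and is the predictor in Question 7 (Section 19.1).
- **Existing washouts.** Section 8.1 postpones the Pre-Study Visit in this case: "If the participant has received antibiotics within 14 days, or a vaccination within 28 days of the planned Pre-Study Visit". Its stated purpose is consistency at baseline. Section 9 applies a two-week antibiotic and a 28-day vaccination washout to later visits. Neither section mentions colonoscopy. The allowance in Section 8.1 for other circumstances concerns booking the Pre-Study Visit, not Baseline.
- **Less definite text.** Section 5.2.1 accepts that some participants may be well into follow-up before they have a colonoscopy. The Phase 2 summary table in Section 9.1.4 gives no timing for Stream 2. Section 27 lets Streams 1 and 3 have endoscopy at any point in the study.

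**The concern.** The primary objective is to describe how the gut microbiota changes from t=0. For one recruitment stream, the schedule puts a bowel procedure immediately before that reference sample. The protocol postpones visits for two other exposures and excludes regular laxative users (Section 7.5), but it sets no order or interval for the one gut procedure that its own schedule places just before t=0.

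If the procedure disturbs the stool microbiota and the disturbance fades, the recovery enters the data as movement between Baseline and later visits. It would look like change with ageing. The same samples would add error to the baseline predictor in Question 7. A later analysis plan can adjust for or drop these samples, but it cannot supply a pre-procedure sample that was never collected.

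**Working it through.** The protocol gives no figure of its own on this point, so there is nothing to reproduce. The check reads the schedule and then scales an assumed effect.

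**1. Gap between colonoscopy and Baseline stool**
- Pre-Study Visit to Baseline: up to 3 weeks × 7 = 21 days, stated as approximate (Sections 9.1.1 and 27).
- The Stream 2 colonoscopy falls inside that window (Section 27), and the stool falls within about a day of Baseline (Section 13.1.2).
- Result: a gap of about 0 to 21 days, with no lower limit stated. The existing washouts are 14 days (antibiotics) and 28 days (vaccination).

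**2. Share of Baseline samples affected**
- The protocol gives no Stream 2 total. It plans 90 biopsy participants, 30 from each cohort (Section 27, footnote 10).
- Assumption: this subgroup is filled from Stream 2. Some support comes from angiography scans being assigned to subgroup 1 in Section 11.3.3 and to Stream 2 in the Section 27 footnotes.
- Share = 90/360 = 25% overall and 30/120 = 25% in each cohort.

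**3. Effect on the overall baseline mean**

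Formula: shift in mean = share affected × shift in an affected sample. The shifts are assumptions, in SD of a microbiome feature. A 50% share shows the sensitivity to a larger Stream 2; a smaller share reduces the effect in proportion.

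| Assumed shift | Share 25% | Share 50% |
|---|---|---|
| 0.2 SD | 0.05 SD | 0.10 SD |
| 0.5 SD | 0.125 SD | 0.25 SD |
| 1.0 SD | 0.25 SD | 0.50 SD |

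As a yardstick, the standard error of a mean of 360 is 1/√360 = 0.053 SD. At a 25% share the three shifts are about 0.9, 2.4 and 4.7 standard errors (0.05/0.053, 0.125/0.053, 0.25/0.053). If the disturbance has gone by the 6-month visit, the same amount appears as change, with opposite sign.

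**4. Is there room to collect the stool first?**
- The routine mailing goes out 10 weeks before the colonoscopy and the study pack follows within days (Section 7.2). The Pre-Study to Baseline window is 3 weeks, so 10 − 3 = 7 weeks remain for reply, telephone contact and booking.
- The stool pack is already in the participant's hands from the Pre-Study Visit (Section 11.8), and the surveillance team shares the date of the next colonoscopy (Section 7.2).

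**The case against.** **The causal step is not in the protocol.** It nowhere mentions bowel cleansing or says that colonoscopy alters stool microbiota, and it gives neither size nor duration for any shift. If recovery takes only days, a gap near 3 weeks could leave little effect. The laxative exclusion concerns regular use, not a single procedure. This stands: the disturbance is an assumption and the table above is a range, not an estimate. What does not depend on it is the absence of any rule on order or interval.

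**Spurious differences between cohorts.** A reader might infer these because recruitment stream is linked to cohort. With Stream 2 shares of, say, 40% and 10% and a 0.5 SD shift, the difference would be 0.5 × (0.40 − 0.10) = 0.15 SD. The documents do not support those shares. Stream 2 may feed all three cohorts (Section 7.2). With the planned 30 per cohort filled from Stream 2, the difference is 0.5 × (0.25 − 0.25) = 0. Cohort 3 is to come mainly from the mental health trust's clinical teams (Section 5.1), so unequal shares are possible, but no split is stated and no figure can be given.

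**Clean samples in the other streams.** A reader might also take Streams 1 and 3 as undisturbed at Baseline. That is not guaranteed, since their endoscopy can fall at any time.

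**One cell of one table.** Sections 5.2.1 and 9.1.4 do not fix the Stream 2 timing in the same way. This is fair and is a reason to reconcile them. Section 27 remains the only place that states a timing specific to Stream 2.

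**Analysis can deal with it.** The outcome is descriptive over nine time points, colonoscopy dates could be traced through hospital notes (Section 11.1), and covariates are left to later analysis plans (Section 19.1). Flagging and sensitivity analysis can indeed be planned later. The order of collection cannot, and dropping the flagged samples would remove t=0 from the participants on whom Section 11.3.3 expects the most gut microbiome information.

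**Conclusion.** The point holds as a scheduling gap. Followed as written, Section 27 places the Stream 2 t=0 stool about 0 to 21 days after colonoscopy, and nothing sets a minimum interval, asks for a pre-procedure sample or marks the samples affected.

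Its size cannot be taken from the documents. It rests on two assumptions: that the procedure and its usual cleansing shift the stool microbiota temporarily, and that subgroup 1 is filled from Stream 2. With both, shifts of 0.2 to 1.0 SD move the overall baseline mean by 0.05 to 0.25 SD, and recovery could be read as change over time. A between-cohort bias would need Stream 2 shares that differ by cohort, which the protocol does not state. The change is worth making because it protects the reference point of the primary outcome at small cost and cannot be made after collection.

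**What to change.** Leave the routine-care colonoscopy where it is and change only the study's sampling rules:

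1. Schedule the Stream 2 Baseline stool before any preparation for the colonoscopy where possible. Where that is missed, collect it after a pre-set interval that the protocol states and justifies.
2. Record the date of any colonoscopy at every visit, for all three streams, because later samples in any stream can also follow a procedure.
3. Flag every stool sample that falls within the interval after a colonoscopy, and exclude flagged samples in a sensitivity analysis.
4. Reconcile the Stream 2 timing in Section 27 with Sections 5.2.1 and 9.1.4.

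Cost: schedule wording and one case report form field. There are three practical downsides. Some stool samples will be separated from the Baseline blood and cognitive measures. Some will come from people whose eligibility is not yet confirmed, since scoring takes 5 to 10 working days and packs are retrieved from those whose cohort is already full (Section 8.2). Where the interval is used instead, some Baseline Visits will be later.

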## 7.2 Stream 2 Participant Identification

The BCSP has a process whereby any patient who is identified as requiring further bowel investigation (either from a flexible sigmoidoscopy or a positive FOBt) is invited for an initial colonoscopy as part of the BCSP as described in Section 5.2.1.

As part of routine care, the BCSP team post a NHS health questionnaire to their patients who are on the 1 and 3 year CSP waiting list 10 weeks in advance of their colonoscopy appointment and request that this is posted back to BCSP team. Within this envelope will be a Study Introduction Letter (Annex 3) which briefly introduces the MOTION study and explains that the MOTION Study PIL, Summary PIS and Full PIS will be posted to them within a few days. There will also be a free post envelope for the participant to send the Stream 2 reply sheet (Annex 8.2).

The CSP Health Questionnaire and the MOTION Study information will be sent separately in case of confusion with return envelopes. The MOTION study envelope will have a MOTION Study sticker placed on the back of the envelope so that this prompts the participant to place the study reply sheet in to this envelope.

The Study Researcher will inform the CSP team which of their patients have responded to the study and subsequently given written informed consent for the study. This is so that the CSP team can inform the Study Researcher of when the next routine care colonoscopy will be due as part of the routine CSP (the participant will have consented to this sharing of information between the Study Researcher and the CSP). For non-responders to the study, the CSP team will not contact their patients again for study purposes.

At the point of consenting, it will not be known if any participant from stream 2 has any inflammatory bowel condition (Ulcerative Colitis, Crohn's Disease or Diverticulitis). Following the routine care colonoscopy, if a participant is found to have any of these conditions, they will not be withdrawn from the study.

Stream 2 will potentially identify participants for cohorts 1, 2 & 3 (Figure 3).

The current number of patients (as at January 2019) on the waiting list for a scheduled colonoscopy as part of the CSP are as follows: -

01/01/2019 – 31/12/2019

494 patients due for 1 or 3 year surveillance (1 year surveillance patients, only until June 2019).

01/01/2020 – 31/12/2020

531 patients due for 3 year surveillance.

01/01/2021 – 31/12/2021

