## 8.2 Pre-Study Visit.

It is acknowledged that the Pre-Study Visit is a lengthy process (up to 2.5 hours) so the Study Researcher will schedule in regular comfort breaks that are convenient for the participant. The Study Researcher will follow the structure of this visit as described above.

The Study researcher will go through the consent form with the participant and encourage any questions they may have at this stage; after which the participant will sign the consent form agreeing to participate in the study.

After completing the Informed Consent process (see Sections 11.1), a copy of the completed Study Consent and Biorepository Consent (if applicable) (see section 11.2) will be given to the participant. Copies of all completed consent forms will be posted to the participant if the participant is from Stream 3.

Following completion of the Cognitive Test (mini-ACE) and the associated questionnaire (CCI), the participant will be provided with their Baseline Visit stool collection pack. See Section 11.3.1 for a full description of the Cognitive tests and associated questionnaires. It will be explained to the participant that within 5-10 working days, the anonymised Cognitive Tests will be scored by [name] or an experienced Research Assistant within his team, or a member of the Study Research Team to ascertain whether the participant is within the required threshold to be included in the study (see Section 11.3.1 for scoring thresholds).

The participant will then be contacted by the QIB Study Researcher to confirm their final eligibility, by telephone by prior arrangement. If their score does not fall within the required threshold, they will be thanked for their time and interest in the study

(Section 16). If the participant feels worried or anxious because they have any concerns, the Study Researcher will act sensitively and reassure the participant that the tests are for research purposes and are not indicative of any clinical diagnosis. Copies of the completed tests will be routinely sent to their GP (Annex 25) if the participant wishes to discuss them.

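### Annex A opens the Stream 2 endoscopy window before eligibility is confirmed, and no text expressly holds the research biopsies until it is

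*Protocol*

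**What the plan says.** **Timing of the endoscopy.** In Annex A (Section 27), the biopsy row for Stream 2 reads "Stream 2 Endoscopy between Pre-Study Visit and Study Collection (Baseline". The Baseline column of the same table is timed "Up to 3 weeks from Pre-Study Visit".

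**Timing of eligibility.** Consent is signed and the mini-ACE and CCI are taken at the Pre-Study Visit. Section 8.2 says that "within 5-10 working days, the anonymised Cognitive Tests will be scored". The scorer may be the named investigator, a research assistant "or a member of the Study Research Team to ascertain whether the participant is within the required threshold". Only then: "The participant will then be contacted by the QIB Study Researcher to confirm their final eligibility". The call has no stated time limit.

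**Ways to fail after consent.** Sections 8.2, 11.3.1 and 16 withdraw a consented person whose scores fall outside the thresholds or whose cohort already holds 120.

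**The biopsies.** Section 5.2.1: "Participants in this study will have, in addition to any routine clinical care biopsies, and when possible 6-8 pinch biopsies". The only order it sets is that research biopsies come after any routine ones.

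**Notice to the colonoscopy team.** Under Section 7.2 the study team tells the surveillance team "which of their patients have responded to the study and subsequently given written informed consent for the study", so that it can learn when the next colonoscopy is due. Section 5.2.1 separately says that the screening team will be told of every enrolled participant. The surveillance mailing goes out "10 weeks in advance of their colonoscopy appointment".

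**The concern.** The window for an invasive research procedure starts at the visit where the eligibility tests are taken, not at the point where their result is known. If a routine colonoscopy falls early in that window, a person who has consented but has no confirmed place could have 6-8 research biopsies and then be told that they are not in the study.

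That person would have undergone an unneeded research step. The tissue would not count toward the 30 per cohort that Section 5.2.1 requires. The routine colonoscopy and any routine biopsies are NHS care and are not in question.

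The other research sampling does not have this gap. Section 8.2 books the Baseline Visit only for people confirmed eligible. Annex A starts stool and blood collection at Baseline, and the OCT and MRI scans follow it. The most invasive sample is the only one whose window opens before the result is known.

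**Working it through.** The plan gives no figure to reproduce here. The check compares two timelines and then looks for a rule that keeps them apart.

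**1. Length of the window.** From the Pre-Study Visit (day 0) to Baseline, up to about 3 weeks (Section 9.1.1 and Annex A): 3 × 7 = 21 days.

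**2. Time until eligibility is known.** Section 8.2 gives 5-10 working days for scoring. From any weekday, ignoring public holidays:
- 5 working days = 7 calendar days
- 10 working days = 14 calendar days

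The wording sets an upper limit, so same-day scoring (0 days) is possible. The confirming call adds an unstated amount.

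**3. Share of the window in which eligibility may be unknown,** before any delay to the call:
- scored at once: 0/21 = 0%
- scored at 5 working days: 7/21 = 33%
- scored at 10 working days: 14/21 = 67%

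These are shares of calendar days, not of people.

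**4. Ways in which a consented Stream 2 person can be turned away.** Section 7.2 says that Stream 2 may feed all three cohorts, so both routes apply.
- Full cohort: 120 already recruited.
- No matching cohort. By the Section 11.3.1 thresholds, cohort 1 is mini-ACE of 26 or more with CCI under 16; cohort 2 is mini-ACE of 26 or more with CCI of 16 or more; cohort 3 is mini-ACE under 26 with CCI of 16 or more. The fourth combination, mini-ACE under 26 with CCI under 16, has no cohort.

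**5. Is there a gate?** The candidates are:
- Section 5.2.1, order of biopsies: research after routine. Eligibility is not mentioned.
- Section 7.2, notice to the surveillance team: triggered by written consent, for the purpose of learning the colonoscopy date. It neither authorises biopsies nor holds them.
- Section 5.2.1, notice of enrolled participants: this would be a gate if *enrolled* always meant confirmed eligible. Section 8.2 uses it that way, saying that people turned away did not meet the threshold to be enrolled. Section 5.2.2 uses it both ways: for people placed in cohort 3, and for everyone at the point of consent, before the cohort is known.

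None of these expressly makes the biopsies wait.

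**6. Can the sequence be put right within the existing timetable?** A Pre-Study Visit held 14 to 21 days before the colonoscopy allows the full 10 working days for scoring. It also keeps the colonoscopy inside the Annex A window, with up to 21 − 14 = 7 days for the call. The mailing lead is 10 × 7 = 70 days, so even a visit 21 days ahead leaves 70 − 21 = 49 days for the study information to arrive, the reply and the telephone screen.

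**The case against.** The strongest reply is that the protocol already implies the right order. Phase 1 is screening and Phase 2 is sampling. Biopsy is not among the Pre-Study Visit activities, and its Annex A row sits under Phase 2. Section 5.2.1 speaks of participants in the study and defines the subgroup by cohort, which presupposes that a cohort has been assigned. It also has the screening team told who is enrolled, and Section 8.2 links enrolment to passing the threshold. On that reading, Annex A merely places the procedure between two visits.

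This has weight. It means that a reader should not infer that the colonoscopy team would never learn who is confirmed, or that the protocol authorises biopsy on consent alone. The notice in Section 5.2.1 may do that work, and the notice in Section 7.2 serves a different purpose. But the gate is only implied. The Stream 2 cell itself begins at a Phase 1 visit, *enrolled* is used in both senses, and *participant* is used from the telephone stage onward.

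A reader might also infer from Section 16 that tissue from a person turned away would be analysed by default. The text does not establish this. The rule that samples are kept unless destruction is requested is stated through Annexes 28 and 30, whereas threshold and full-cohort exclusions cite Annex 26. Whether the rule reaches these people is unclear.

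Other limits also stand. Consent precedes the window, so this is not biopsy without consent. The 10-week lead makes early scoring possible. The figure in the Stream 2 section and the one summarising Phase 1 are not available here and could show a sequence.

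**Conclusion.** The point holds in a limited form. As written, Annex A permits research biopsies before final eligibility and cohort place are known, and no available text expressly prevents it. This goes beyond missing detail, because the stated window itself allows the wrong order.

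Its size in people cannot be determined. The protocol gives no turn-away rate for Stream 2, no distribution of colonoscopy dates within the window and no actual scoring times. What can be bounded is exposure in time: 0 to 14 of about 21 days, or 0% to 67%, plus any delay to the call. The upper figure assumes the full scoring allowance, a full 3-week window and no public holidays. It should not be read as the chance that a person is affected. People whose colonoscopy falls after Baseline, which Section 5.2.1 allows for, are not affected.

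The reason to act is protection of participants. An effect on the analyses is possible but not shown.

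**What to change.** 1. In Section 5.2.1 and Annex A, state that research biopsies are taken only after final eligibility and cohort place are confirmed. The routine colonoscopy goes ahead regardless.
2. Score the mini-ACE and CCI before the colonoscopy date. Use the 10-week lead to hold the Pre-Study Visit early enough, or prioritise scoring when the date is close; Section 8.2 already lets a study team member score.
3. Make the notice to the colonoscopy team in Sections 5.2.1 and 7.2 state confirmed eligibility, not only consent or enrolment.
4. Optionally, clarify in Section 16 that samples from people excluded at the Pre-Study step are not used in the cohort analyses.

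The cost is about a sentence in each place, prompt scoring of two tests that take about 5 minutes each to complete, and one clear notice per Stream 2 participant with a pending colonoscopy. The downside is that a few late responders lose their first research-biopsy opportunity. This is a cheap improvement.
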